#### Microbiological evaluation

This is one of the primary outcomes of the study. A sample of caries-affected dentin will be taken from each selected tooth before the removal of the carious tissue. The samples will be standardized with the use of a Meyhoefer auricular curette n° 2 (ABC Instrumentos Cirúrgicos, São Paulo, Brazil), because it has a hole in its tip, and placed into test tubes containing 3.8 ml of the transport medium (Phosphate Buffered Saline (PBS) - Thermo Fisher Scientific, Massachusetts, EUA). The dental tissue will be dispersed in the transport tube (Microtubo Tipo Eppendorf Cap. 1.5 ml – GlobalPastic, São Paulo, Brazil) containing glass pearls through agitation at maximum speed in a vortex device (Agitador Para Tubos Vortex – Kasvi, Paraná, Brazil) for 30 s to homogenize the biological material. The biofilm will be diluted in series on the order of 10^1^ to 10^6^ in peptone water and inoculated in culture media in Petri dishes (Placa de Petri Descartável Estéril - PRO-LAB MATERIAIS PARA LABORATORIOS LTDA, São Paulo, Brazil). Aliquots of dilutions 10^4^, 10^5^, and 10^6^ will be sewn on the surface of Brucella agar (Difco Laboratories, Detroit, Michigan) containing defibrinated sheep blood (50ml/L), hemin (5 mg/ml), and menadione (10mg/ml) for the determination of the total number of viable microorganisms (VM). Aliquots of dilutions 10^3^ and 10^4^ will be sewn on Mitis Salivarius agar (Difco Laboratories, Detroit, Michigan) for the determination of the total number of streptococcus (S). Aliquots of dilutions 10^1^ and 10^2^ will be sewn on Mitis Salivarius agar with the addition of debacitracin for the determination of the population of streptococcus of the mutans group (SM).

Aliquots (100 ml) from each dilution will be sewn onto the surface of agar and spread with the aid of a Drigalski spatula. Undiluted aliquots and aliquots from dilution 10^2^ (100 ml) will be pour-plated on Rogosa SL agar (Difco Laboratories, Detroit, Michigan) for the determination of lactobacilli (LB). The Brucella agar dishes will be incubated in an anaerobic chamber (PLAS by LABS, Lansing, MI) at 37°C for 7 days. The Mitis Salivarius agar and Mitis Salivarius Bacitracin dishes will be incubated in a 10% CO_2_ atmosphere (CO_2_ greenhouse, Shel Lab, mod. 2123, Oregon) at 37°C for 48 h. The dishes containing Rogosa agar will be incubated in a 10% CO_2_ atmosphere at 37°C for 72 h. After incubation, the characteristic colonies in each dish will be counted with the aid of a stereomicroscope at a magnification of 10 times in dilutions with 30 to 300 colonies per dish. All procedures will be performed in duplicate, and the mean of the counts will be calculated. The results will be expressed in colony-forming units (CFU) of SM and LB as well as in proportion of streptococcus (% S/VM), SM group (% SM/VM and lactobacilli (% LB/VM) in relation to the total of viable microorganisms (VM). For SM, the proportion in relation to the total of streptococci (% SM/S) will also be calculated. Immediately after the removal of the carious tissue, samples of the remaining dentin will be taken with a Meyhoefer auricular n° 2 curette and the procedures will be repeated [14].

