### Methods in analysis to handle protocol non-adherence and any statistical methods to handle missing data {20c}

No losses greater them 5% of the sample are expected, and if they happen, pairwise deletion will be used.

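### Lactobacilli are plated only undiluted and at 10^2 under a 30–300 colony rule, so a tenfold range of counts has no countable dish, and the fixed dilutions keep count floors in place after treatment

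*Protocol article*

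**What the plan says.** All of the laboratory rules are in the protocol article under Microbiological evaluation.

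- Series prepared: "The biofilm will be diluted in series on the order of 10^1^ to 10^6^ in peptone water".
- Total viable microorganisms (VM): "Aliquots of dilutions 10^4^, 10^5^, and 10^6^ will be sewn on the surface of Brucella agar".
- Total streptococci (S): "Aliquots of dilutions 10^3^ and 10^4^ will be sewn on Mitis Salivarius agar".
- Mutans streptococci (SM): "Aliquots of dilutions 10^1^ and 10^2^ will be sewn on Mitis Salivarius agar with the addition of debacitracin".
- Lactobacilli (LB): "Undiluted aliquots and aliquots from dilution 10^2^ (100 ml) will be pour-plated on Rogosa SL agar".
- Counting rule: colonies are "counted with the aid of a stereomicroscope at a magnification of 10 times in dilutions with 30 to 300 colonies per dish".

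Everything is done in duplicate and averaged. The same procedure is applied to the dentin sample taken after caries removal, and no other dilutions are named for it. Results are CFU of SM and LB, plus four proportions: S, SM and LB relative to VM, and SM relative to S. The microbiological evaluation is one of the primary outcomes (Outcomes {12}).

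The article does not say what is recorded when no dish falls within 30 to 300 colonies. Its only missing-data rule, in section {20c}, is that if losses exceed 5% of the sample, "pairwise deletion will be used".

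**The concern.** A counting window of 30 to 300 colonies spans one factor of ten, so consecutive tenfold dilutions join end to end. VM, S and SM are plated at consecutive dilutions. LB skips one, which leaves a hole in the middle of its range, although LB CFU is a named result within a primary outcome.

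The lowest plated dilution also sets a floor for each medium. The treatments are meant to lower the counts, yet the second sample is plated at the same dilutions as the first. SM or LB counts below their floors have no CFU value. If VM is below its floor, three of the four proportions have no usable denominator.

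Whether a value can be determined therefore depends on the value itself. How to analyse such values can be left to an analysis plan, but no analysis can recover a dish that was never poured.

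**Working it through.** **Inputs from the article:** 30 to 300 colonies per dish; plated dilutions as listed above; 3.8 ml of transport medium.

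**Assumption:** 0.1 ml plated. The text reads "Aliquots (100 ml) from each dilution will be sewn onto the surface of agar", but 100 ml cannot be drawn from a 3.8 ml sample, and a micro sign may have been lost. If 100 ml were literal, every limit below would be 1,000 times lower; the width of the LB gap would not change.

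**Readable window for dilution 10^k:** from 30×10^k/0.1 to 300×10^k/0.1 CFU/ml.

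| Medium target | Dilutions plated | Readable range, CFU/ml | Gap |
|---|---|---|---|
| VM | 10^4, 10^5, 10^6 | 3×10^6 to 3×10^9 | none |
| S | 10^3, 10^4 | 3×10^5 to 3×10^7 | none |
| SM | 10^1, 10^2 | 3×10^3 to 3×10^5 | none |
| LB | undiluted, 10^2 | 3×10^2 to 3×10^3 and 3×10^4 to 3×10^5 | 3×10^3 to 3×10^4 |

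**LB gap.** With c colonies expected undiluted, the 10^2 dish expects c/100. No dish qualifies when c > 300 and c/100 < 30, that is, for c from 301 to 2,999. The width is 3,000/300 = 10, and the volume cancels. Duplicates repeat the same two dilutions and do not fill it.

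**Which teeth fall in the gap.** From an LB baseline of 10^5 CFU/ml (illustrative), a 1-log fall to 10^4 is unreadable, a 2-log fall to 10^3 is readable, and a 3-log fall to 10^2 is below the floor.

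**How many teeth.** The article gives no loads, so this is assumption only. With lognormal LB, mean log10 of 3 to 5 and SD 1, 24–38% fall in the gap and 1–30% below the floor. With post-treatment VM of mean log10 6 to 7.5 and SD 1, 15–68% fall below the VM floor. For scale, Sample size {14} recruits 40 per group for a minimum of 34, a margin of 6/40 = 15%.

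**What deletion would do, if it were applied.** For log10 counts with mean μ and SD 1, the mean of those kept in a window (a, b) is μ + [φ(a−μ) − φ(b−μ)]/[Φ(b−μ) − Φ(a−μ)]. The SM window runs from log10(3×10^3) = 3.477 to log10(3×10^5) = 5.477.

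- Arm means 4.5 and 3.5: 68% and 49% of teeth kept; means of those kept 4.48 and 4.21. A true difference of 1.0 log becomes 0.28.
- Arm means 4.0 and 3.0: 63% and 31% kept; 4.34 and 4.09. The difference becomes 0.25.
- With the floor alone (b infinite), the differences are 0.50 and 0.37.
- Deleting only values in the LB gap, in the same two scenarios, turns 1.0 into 1.48 and 1.31. The gap on its own can therefore push the other way.

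**After plating 10^1 for LB.** The added window is 3×10^3 to 3×10^4, which closes the gap exactly. If values outside 3×10^2 to 3×10^5 were still deleted, the difference would be 0.54 and 0.51 in place of 1.0, so the extra plate does not replace a censored analysis.

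**The case against.** A reader might infer that strong responders lose their CFU outcome, that the most effective arm loses most values, and that comparisons are therefore biased towards no difference. The documents do not support this.

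- The LB gap takes intermediate counts, at baseline as well as after treatment. A moderate responder can be lost while a stronger one is counted.
- VM is not reported as a CFU outcome. Its floor costs the three proportions that use it as denominator, not the CFU of SM or LB.
- No bacterial loads or expected log reductions appear in the text, and three of the four arms deliberately leave carious tissue on the pulp floor. Neither a high floor nor a 2- to 3-log fall can be asserted.
- Section {20c} does not say that a dish outside 30 to 300 makes the sample missing. It could be recorded as above or below a limit, and the full protocol or analysis plan may say so.

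All four objections stand, and they limit the consequences that can be claimed. They leave the tenfold gap untouched, because it follows from the stated dilutions and counting rule alone. A further objection also stands: moving the post-treatment plates down would create the opposite problem. Brucella agar at 10^2 to 10^4 would have a ceiling of 300×10^4/0.1 = 3×10^7 CFU/ml instead of 3×10^9. Mitis Salivarius at 10^1 and 10^2 would stop at 3×10^5, which is the present S floor.

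**Conclusion.** The point holds in a limited form. It is certain that LB counts have an unreadable range of exactly tenfold, at any plated volume and in both samples. It is also certain that the floors are carried over unchanged to the post-treatment sample; their absolute values rest on the 0.1 ml assumption. SM and LB CFU below their floors, and proportions of VM when VM is below its floor, are undetermined in a way that depends on the count.

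The share of teeth affected cannot be derived from the article. If undetermined values were handled by pairwise deletion, floor losses could shrink differences between arms, as the SM illustration shows. That is conditional, and the direction of any net bias, including the effect of the LB gap, is not established. The plating scheme should be changed while samples remain to be plated, because unread samples cannot be recovered later.

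**What to change.** 1. Plate the 10^1 dilution on Rogosa agar as well. The tube is already in the series, and LB becomes countable without a break from 3×10^2 to 3×10^5 CFU/ml (0.1 ml assumed).
2. State that counts outside the readable range are recorded with their limits and analysed as left-, right- or interval-censored on the log10 scale, for example by censored regression, rather than deleted. This is needed even after step 1: LB is already plated undiluted, so its floor remains.
3. Do not compute a proportion of VM as an exact value when VM is outside its range.
4. If lower dilutions are wanted for the second sample on Brucella or Mitis Salivarius agar, add them to the existing ones so that the upper range is kept.
5. Correct or confirm the plated volume.

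Cost: one extra Rogosa dilution in duplicate per sample, a few more plates if step 4 is taken up, and a sentence or two on recording and analysis.

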#### Radiographic evaluation

This is one of the primary outcomes of the study. The radiographic examinations will be carried out in the following manner: (1) periapical radiographs will be used as a diagnostic aid; (2) after the incomplete removal of the demineralized dentine and the temporary filling of cavity, a bitewing radiograph it will be taken to allow the analysis of the radiolucent zone (RZ), that is, the amount of demineralized dentine left; (3) immediately, 1 week, and 1, 3, 6 and 12 months, periapical and bitewing radiographs will be taken to analyze the integrity of the periapical area and the eventual changes in the RZ.

To obtain geometric standardization of films, bitewing film holders will be used. The images obtained before and after the treatment will be digitized by a ScanJet 6100 scanner Hewllet-Packard (OR, USA). The images will be stored in maximum-quality JPG format. The Imagelab software (version 2.3, SoftiumSistemas de Informatica, São Paulo, Brazil) will be used to analyze the images (equalize and subtract). Change in the density measurement of the RZ during treatment will be evaluated blind through digital subtraction of radiographic images in relation to the initial exams in the experimental periods (immediately, 1 week, and 1, 3, 6, and 12 months).

The radiographic subtraction process will consist of comparing two images. By definition, a digital subtraction image from a site where no change in density has occurred would show a complete cancelation of all anatomical structures, eliminating the constant structures present in both. Any change in the structures indicates a change in density. This method requires standardized radiographs regarding the X-ray projection, exposure time, film, and development. Nonetheless, the procedures will be standardized; radiographs will be performed at different moments, which causes them to have different densities. To correct for any changes in density, the gray-level histograms of the two images will be compared and adjusted using a nonparametric contrast correction algorithm. The image radiograph equalization will be done in the following way: the radiograph taken immediately after the treatment and the one taken after each period of treatment (immediately, 1 week, and 1, 3, 6, and 12 months) will be placed beside one another on the computer screen. The radiograph that shows the best distribution of gray tonalities on the histogram will be chosen as a model, and the other image will be equalized according to the model.

The subtraction will be carried out the following way: the radiograph taken immediately after the treatment and the images obtained after each of the experimental periods will be overlapped. The anatomic details of the two images will be matched by rotation or moving the images horizontally or vertically. The radiolucent zone beneath the restoration and two control areas (CA1 and CA2) will be selected. The control areas will be dentinal areas (mesial and distal) close to the RZ. The difference in radiographic density between the two radiographs will be determined for each selected area using a gray tonalities scale. There are 256 individual shades of gray in an 8-bit pixel going from 0 (black) to 255 (white). This is the pixel’s grayscale resolution. An average gray level value of 128 (the middle of the digitizer gray level range set by the software) would show up at each pixel. Areas with gray levels <128 in the subtraction image would indicate a loss in density and gray levels >128 would indicate an increase in density [15].

#### Evaluation of time required for the procedure (secondary outcome)

The time required for each procedure will be measured using a digital stopwatch (Kenko, Hong Kong) in minutes and seconds from the onset of treatment until the complete removal of the carious tissue. The time will be recorded on a specific chart for analysis. The need or non-need for anesthesia will also be recorded.

#### Evaluation of the need for local anesthesia during intervention and degree of pain/discomfort of children during the procedure (secondary outcome)

All interventions will be initiated without the prior administration of local anesthesia. The children will be told that anesthesia could be administered at any time during the intervention. A face scale with different expressions will be used to evaluate the need for local anesthesia and the child will be asked to point to the expression that most corresponds to his/her degree of pain/discomfort.

Interpretation of face scale:No pain.Mild pain.Moderate pain.A little worse pain.Strong pain.Worst pain.

#### Clinical evaluation

This is one of the primary outcomes of the study. The clinical evaluation will be performed by a researcher blinded to the different treatment groups. The criteria used for the evaluation will be the retention of the restorative material in the cavity and the occurrence of secondary caries. The evaluation scores will be based on the criteria below. Digital photographs of the restorations will also be taken and serve to complement the clinical and radiographic findings. The visual demonstration will contribute to any necessary clarifications and facilitate the discussion and documentation of the cases. Thus, digital photographs will be taken of all teeth in the different groups before and after the interventions. We believe participants will be present for the follow-ups due to concerns and other possible treatments in the clinic.0 = present; no defects;1 = present; small marginal defects measuring less than 0.5 mm in depth; no need for repair;2 = present; small marginal defects measuring 0.5 mm to 1mm in depth; need for repair;3 = present; large marginal defects measuring 1 or more mm in depth; need for repair;4 = absent; restoration nearly or completely lost; need for treatment;5 = absent; additional treatment having been performed for some reason;6 = tooth absent for any reason;7 = present; surface wear measuring less than 0.5 mm in depth; no need for replacement;8 = present; surface wear greater than 0.5 mm in depth; need for replacement; and9 = impossible to diagnose.

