#### Specific objectives

To investigate the efficacy of photodynamic therapy with *Bixa orellana* and Papacarie™ with regard to microbiological (counting of colony-forming units before and after treatments – CFU), radiographic (integrity of the periapical area and eventual changes in the radiolucent zones), and clinical aspects (retention of the restorative material in the cavity and occurrence of secondary caries) (primary objective);To evaluate the antimicrobial effect of aPDT on caries-affected dentin in permanent teeth (secondary objective);To perform a radiographic evaluation of the remaining dentin and radiographic density at 6 evaluation times, over a 12-month period (secondary objective); andTo evaluate the need for local anesthesia during intervention and the degree of pain/discomfort (with a face scale) of children during the different procedures (secondary objective).

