### Outcomes {12}

For the treatment of caries lesions to be considered successful, it should be able to remove infected tissue and microorganisms in a sufficient amount, so that, in the control session, the teeth that were once infected do not show any signs of remaining infected tissue beneath the restorative material. Consequently, the microbiological evaluation had been chosen as the primary outcome. However, factors such as the radiological exam and the clinical aspects are also important for the control section, to show the presence or lack of success. Therefore, the microbiological, radiographic, and clinical evaluations should be considered as primary outcomes.

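### Secondary caries is a named part of the primary clinical outcome, but no code on the 0–9 scale fixed for that outcome records it, and no other section defines it

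*Protocol article*

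**What the plan says.** Specific objectives {7} puts secondary caries inside the primary objective: "clinical aspects (retention of the restorative material in the cavity and occurrence of secondary caries) (primary objective". Outcomes {12} confirms the rank of the clinical assessment: "Therefore, the microbiological, radiographic, and clinical evaluations should be considered as primary outcomes".

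The Clinical evaluation subsection names the two things to be judged: "The criteria used for the evaluation will be the retention of the restorative material in the cavity and the occurrence of secondary caries". It then fixes the instrument: "The evaluation scores will be based on the criteria below". A complete list of ten codes follows, starting with "0 = present; no defects;1 = present; small marginal defects measuring less than 0.5 mm in depth; no need for repair" and including "5 = absent; additional treatment having been performed for some reason;6 = tooth absent for any reason" and "8 = present; surface wear greater than 0.5 mm in depth; need for replacement". The assessor is blinded to group.

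Three other elements touch the same ground:

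- The group descriptions under Intervention description {11a} schedule a clinical check for infiltration and radiographs from immediately after treatment to 12 months.
- The Radiographic evaluation subsection schedules periapical and bitewing films at the same times and measures grey-level change in the radiolucent zone beneath the restoration.
- Photographs are taken as supporting documentation.

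**The concern.** The outcome has two components and the scale printed for it can express only one. Whether the filling survives can be read from the codes. Whether new caries has developed cannot.

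This matters more here than in an ordinary restoration study. Groups 2, 3 and 4 leave carious dentin on the pulp floor by design and group 1 does not, so the rate of later caries could differ between arms. If it does, a scale that grades only the filling would not show it. Findings not written down at a visit may also be hard to recover later. The primary objective would then be reported on restoration survival alone, with no secondary-caries variable behind it.

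**Working it through.** The plan gives no figure on this point, so the check is to set the stated outcome beside the stated measures.

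**Step 1. What each code can express** (Clinical evaluation, score list)

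| Codes | Content | Identifies caries? |
|---|---|---|
| 0 | Restoration present, no defect | No |
| 1–3 | Restoration present, marginal defect graded by depth | No |
| 4 | Restoration lost or nearly so | No |
| 5 | Further treatment given, reason not specified | No |
| 6 | Tooth absent, reason not specified | No |
| 7–8 | Restoration present, surface wear graded by depth | No |
| 9 | Cannot be diagnosed | No |

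Codes that identify caries: 0 of 10.

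**Step 2. Where a carious tooth would fall.** Take a tooth whose restoration is present, with no marginal defect and no wear, and with caries beside it. Codes 1–3 need a marginal defect, 7–8 need wear, and 4–6 need a loss or further treatment. Among the codes for a restoration that is present, only 0 is left. An examiner might instead choose 9, or 5 once the tooth had been re-treated. None of these choices marks the tooth as carious.

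**Step 3. Whether another section supplies the variable**

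- Infiltration check ({11a}, all four groups): scheduled, but with no grade, no definition and no stated link to secondary caries.
- Radiographic subtraction: a primary outcome of its own. It yields a grey-level change in the radiolucent zone, and the protocol describes that zone as the demineralised dentin left behind. No rule turns a density change into new caries.
- Photographs: no caries criterion attached.
- Plans for assessment {18a}: requires a kappa above 0.85 for the clinical and radiographic evaluations. Kappa needs defined categories, and secondary caries has none.
- Outcomes {12}, opening paragraph: describes success as no sign of infected tissue remaining under the restoration. It sets no cut-off on the codes and does not define secondary caries.

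**Step 4. Scale, under an assumption.** The documents give no secondary-caries rate. Assume 5% to 15% of teeth are affected with the restoration still present, and use the 34 teeth per group from Sample size {14}:

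- 0.05 × 34 = 1.7 teeth
- 0.15 × 34 = 5.1 teeth

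That is about 2 to 5 teeth per group.

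**Step 5. What a comparison could show.** Take the two ends of that range as two arms, 5% against 15%:

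- Standard error of the difference with 34 per arm: √(0.05 × 0.95/34 + 0.15 × 0.85/34) = √(0.00140 + 0.00375) = 0.072.
- 95% half-width: 1.96 × 0.072 = 0.14, or 14 percentage points around a 10-point difference.
- Power of a two-sided Fisher exact test at 5%, summed over all binomial outcomes: about 13% with 34 per arm and about 18% with 40 per arm.

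The sample size was set on CFU, so a secondary-caries comparison would be imprecise even with perfect recording.

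**The case against.** The strongest reply is that secondary caries is not ignored. A blinded researcher is told to judge it, infiltration is looked for at every follow-up in every group, and bitewing and periapical films are taken at each time point. Subtraction beneath the restoration could show density loss. A yes/no box on a case report form is also the kind of detail a journal article may leave to the full protocol.

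Much of this stands. A reader might infer that secondary caries goes unobserved at every visit. The documents do not support that: it is to be looked at, but has no code or definition. The condensation argument does not rescue the text, however. The scale is printed in full and presented as the scoring basis for both criteria, so this is a mismatch between outcome and instrument and not an omitted detail.

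Three further inferences also go too far:

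- *That such teeth will be scored 0.* No rule says so. Code 0 is the one that fits a sound, unworn restoration, but an examiner could choose another.
- *That recurrent caries is counted as success.* No code is labelled success, and the opening paragraph of Outcomes {12} points the other way.
- *That a false finding of no difference is likely.* This would rest on an assumed rate, and Step 5 shows that the comparison would probably be inconclusive even with complete recording.

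**Conclusion.** The point holds as a mismatch inside the current text: a named component of a primary outcome has no code on the scale fixed for that outcome and no definition or grade elsewhere. If the plan is followed as written, that part of the primary objective has no analysable variable. This conclusion needs no numerical assumption; it follows from reading the ten codes against the stated criteria.

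Its reach is limited. The microbiological outcome, the radiographic outcome and the retention part of the clinical outcome are unaffected, and no sample-size figure changes. The 2 to 5 teeth per group depends wholly on the assumed 5% to 15% and indicates scale only. The direction and size of any effect on the comparison between arms cannot be determined from the documents.

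**What to change.** At each scheduled follow-up visit, have the blinded clinical examiner who is already planned record secondary caries as a separate present/absent item beside the 0–9 code.

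Write the definition before it is used. It should draw on both the clinical inspection and the radiographs already taken, because a check of the margin alone would miss a lesion under an intact filling. It should also state how new caries is told apart from the carious floor dentin left by design in groups 2–4; without that, the item would tend to reflect group membership.

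Report the proportion of teeth with secondary caries by 12 months in each arm and compare arms on it as its own outcome, not derived from the 0–9 code. Give confidence intervals, and say that precision will be low because the sample size was set on CFU.

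The cost is one extra form field and one extra comparison, plus the work of agreeing the definition. It needs no new visit, film or examiner and changes no treatment.
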